**Objective 3.1.2: Estimate the cost and cost effectiveness the PrEP and TasP demonstration project.**

A critical aspect of implementation is to obtain estimates of the cost of implementing PrEP on a small scale. Incremental financial and economic costs of provision will be collected from the provider's perspective for the duration of the demonstration project. Financial costs represent actual project expenditures, while economic costs represent the full value of all resources used in the intervention. Effectiveness will be modelled based on the Nigerian epidemic and intermediate demonstration trial outcomes to provide life years gained and infections averted. These will be matched with costs to estimate the cost effectiveness of the intervention in terms of cost per life year gained and cost per infection averted. Patient travel and opportunity costs will also be collected. This will provide insights into the travel costs incurred by the project to support transportation of study participants from satellite sites to the main study sites as well as other costs of participation

*The primary measure of this objective is cost per life year gained and cost per infection averted.*

**Objective 3.1.3: Model the resources needed to provide scaled up PrEP and TasP access for serodiscordant couples in Nigeria.**

While objective 3.1.2 will provide insights into the cost-effectiveness at demonstration project scale and target population level, this objective will enable the team make projections on what the real cost of scaling up the project will be. We will model the cost of a national PrEP program targeting serodiscordant couples. Using the cost data generated during the demonstration project, a cost model will estimate the total financial resources needed to scale up to a regional or national program as deemed appropriate. Further analysis will be undertaken to explore non-financial constraints such as personnel and infrastructural constraints.

*The primary measure of this objective is an estimate of the total budget necessary to scale up PrEP and TasP nationally within the various target groups.*

**3.2 Secondary objectives**

- 3.2.1 Assess client, facility and community level factors influencing demand, preferences, uptake and adherence for antiretroviral-based HIV-1 prevention in Nigeria
- 3.2.2 Assess user preferences among high-risk HIV-1 serodiscordant couples for ART initiation for HIV-1 infected partners and PrEP for HIV-1 uninfected partners.
- 3.2.3 Ascertain initiation of and adherence to PrEP among HIV-1 uninfected partners as a bridge to ART.
- 3.2.4 Look for evidence of risk compensation by HIV-1 serodiscordant couples on PrEP or TasP, migration from condom use.
- 3.2.5 Determine the ART resistance profile developed by HIV-1 serodiscordant couples on PrEP during the study; assess that profile's prevalence.
- 3.2.6 Model the resources needed to provide PrEP and TasP for other specific target groups who are also at high risk of contracting HIV.

**Objective 3.2.1: Assess client, facility and community level factors influencing preferences, uptake and adherence for antiretroviral-based HIV-1 prevention in Nigeria**

Understanding factors that influence couples' preferences and their likelihood to initiate and adhere to PrEP and/or ART in a real-world setting is critical for providers who will counsel HIV-1 serodiscordant couples.

Using interviewer-administered questionnaires, assessments will be made of the correlates to preferences, uptake and adherence to ART and PrEP. These will include characteristics of sexual risk (e.g., sexual frequency, condom use, whether the HIV-1 uninfected partner reports outside partners); depression and substance use; gender of the HIV-1 uninfected partner; fertility intentions; partnership characteristics (whether the couple is cohabiting at baseline, has children, is together throughout follow-up, whether members have other partners, and whether the HIV-1 infected partner initiates ART), and clinical characteristics of the HIV-1 infected partner (e.g., CD4 count, WHO stage).

Facility level factors would be assessed. This would include the impact of training on quality of service delivery and perceived changes by clients at the service sites, effective communication strategies, adherence counselling, use of centralized vs decentralized services for drug access, time spent and costs for travels to facility. The study shall also assess the impact of use of home self-test kits (OralQuick®) for partner recruitment and uptake of PrEP and TasP by serodiscordant couples. See the attached Protocol B.

Community level factors to be measured include the role of public communication and the impact of the designed community engagement programme on stigma and perception about the use of PrEP by community members. A specific detailed protocol will be developed to outline the community engagement methodology and the plan to assess the impact of the programme on PrEP uptake and adherence.

*The primary outcome of this objective will be data and assessments about the factors that support or create barriers to clients' use of PrEP and partner's use of TasP.*

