## 2.0 Study Method

This is a demonstration project to evaluate the effectiveness of three models for the delivery of PrEP and TasP as part of a combination prevention strategy for serodiscordant couples in three states in Nigeria. The overall goal is to identify the best model to facilitate uptake of PrEP as part of a comprehensive HIV prevention package for the HIV negative partner in serodiscordant relationships whose HIV positive partner has not begun ART or

---

has been on ART for less than six months. PrEP (daily oral FTC / TDF) will be offered to the HIV-1 uninfected partner. Uptake of PrEP and TasP and adherence to PrEP will be measured. Factors (individual, facility and community level) that facilitate PrEP and TasP uptake and adherence to PrEP will also be assessed.

HIV-1 infected participants will be offered the opportunity to use ART support services regardless of their CD4 count. This is in line with the current national guidelines on HIV treatment for adults and adolescents (2010:13). The current guidelines enable HIV positive individuals in discordant relationships to have access to ART irrespective of the CD4 count. This project will therefore serve as a measure of the effectiveness of this program in Nigeria.

For each couple, if the HIV-1 infected partner initiates ART, we will discontinue PrEP for the HIV-1 uninfected partner six months later (once viral suppression is typically achieved). If the HIV-1 infected partner declines to initiate ART, or initiates and discontinues, we will continue PrEP. Mixed-methods work will be conducted to understand user preferences, couples decision-making, and barriers to uptake of and adherence to both PrEP and ART.

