At enrollment HIV-1 uninfected women will have a pregnancy test to confirm eligibility (must not be pregnant to complete enrollment). Women will be asked about pregnancy at every scheduled follow-up visit and pregnancy testing will be done when clinically indicated (e.g., missed menses, participant request); PrEP will be continued during pregnancy and breastfeeding. In addition, pregnant women will be advised to continue with their follow up visits. When these participants no longer have a positive pregnancy test, the pregnancy outcome will be documented.

Every 6 months, in addition to regular quarterly visit procedures, CD4 counts and plasma viral loads will be done for HIV-1 infected partners.

Clinical safety will be assessed pre-, during- and post-enrollment. Laboratory safety assessments will be done at enrollment, month 12, study exit and additionally if indicated. At these visits, blood samples will be collected for urea, electrolytes, creatinine, liver function tests, full blood count, calcium and phosphate levels.

All HIV-1 infected partners who are interested in starting ART independent of their becoming eligible for ART under the current national guidelines, will be offered ART. Once the HIV-1 infected partner has been using ART for 6 months, PrEP will be discontinued for the HIV-1 uninfected partner, after counseling to the couple.

During follow-up, HIV-1 infected and uninfected participants will complete a quantitative interview to capture evolution in preferences to uptake of antiretroviral-based HIV-1 prevention and fertility intentions and any risk compensation behaviours. Questionnaires will be administered separately to both members of couples.

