### 13.0 Data management and analysis

#### 13.1 Data analysis

A Statistical Analysis Plan (SAP) will be developed. This will outline the planned analyses. Any deviations to be made from the plan will be documented in the SAP.

For the primary objective 3.1.1, the outcome variable to be measured will be the uptake of antiretroviral-based HIV-1 prevention program. Data collected will include all sero-discordant couples recruited into the study and will be followed up longitudinally. The number of new infections averted through the use of PrEP and TasP by sero-discordant couples who accessed the ARV preventions compared with those who had access to programs but did not use the tools will be documented. The impact of various variables such as age, viral load of partner, region, coital act, use of condom on uptake of PrEP and TasP and on HIV sero-conversion will also be assessed.

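### Objective 3.2.1 lists as correlates one variable known only when follow-up ends and one that is itself a listed outcome

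*Protocol*

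**What the plan says.** Under Objective 3.2.1 (Protocol, section 3.2), "assessments will be made of the correlates to preferences, uptake and adherence to ART and PrEP". That gives six outcomes: preference, uptake and adherence, each for ART and for PrEP. The purpose is directional and meant to help counsellors: "Understanding factors that influence couples' preferences and their likelihood to initiate and adhere to PrEP and/or ART".

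One list of characteristics serves all six outcomes. Among the partnership items, cohabitation is dated ("whether the couple is cohabiting at baseline"). The items that follow include whether the couple "is together throughout follow-up, whether members have other partners, and whether the HIV-1 infected partner initiates ART". No correlate is paired with a particular outcome and no model is named.

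Elsewhere the Protocol ties ART initiation to the end of PrEP. Section 2.0 says that "if the HIV-1 infected partner initiates ART, we will discontinue PrEP for the HIV-1 uninfected partner six months later", and section 11.5 says the same: "Once the HIV-1 infected partner has been using ART for 6 months, PrEP will be discontinued for the HIV-1 uninfected partner". Section 11.0 plans visits at month 1 and then quarterly for up to 18 months.

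**The concern.** A correlate of uptake or adherence should be measured before the outcome it is meant to explain, and should not be that outcome under another name. Two listed items fail this test.

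- **Together throughout follow-up.** Its value is fixed only at the end, whereas PrEP is offered at enrolment (section 11.5). It also depends on observation. Section 6.0 limits tracing to safety issues and the end-of-study HIV assessment, so couple status will be less complete in those who stop attending. Section 11.5 ends follow-up of both partners soon after a seroconversion, which leaves such couples less time in which to separate.
- **Index partner initiates ART.** This is ART uptake. For PrEP outcomes it is also the event that, by rule, later stops PrEP, so it determines how long PrEP use can be observed.

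At stake is the reading of a secondary objective intended to inform counselling. Associations that come from the definition of a variable, or from length of observation, could be taken for factors that influence uptake or adherence.

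**Working it through.** The Protocol gives no figure, model or test for this objective, so there is nothing to reproduce. The checks below use its stated rules. Assumptions that are not in the Protocol are marked.

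**1. ART initiation against ART uptake.** Correlate and outcome are the same event. Uptake is 100% in initiators and 0% in non-initiators, whatever the model.

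**2. Together throughout, by length of follow-up.** *Assumption:* separation occurs at a constant rate and reaches a share s by month 18. The share still together over f months is (1 − s)^(f/18).

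| Months followed | s = 10% | s = 20% | s = 30% |
|---|---|---|---|
| 3 | 98.3% | 96.3% | 94.2% |
| 6 | 96.5% | 92.8% | 88.8% |
| 18 | 90.0% | 80.0% | 70.0% |

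With one and the same separation rate, couples followed for less time qualify more often. Anything that shortens follow-up and is related to uptake or adherence will therefore be associated with this variable even if staying together has no effect. If observation of a couple stops at separation, the bias runs the other way for uptake, because separated couples have less time in which uptake can be recorded.

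**3. Partner ART start against PrEP adherence.** PrEP can last at most min(18, t + 6) months if ART starts at month t. Two illustrations assume no true link between ART start and adherence.

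- *Assumption A:* adherence is 80% at all times on PrEP, and pill coverage is counted over all 18 months: 80% × PrEP months / 18.
- *Assumption B:* adherence wanes linearly from 90% to 66% over 18 months and is averaged over PrEP months only. The mean over the first m months is 90 − 24 × m / (2 × 18).

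| ART start | PrEP months | Share of 18 months | A: 18-month coverage | B: mean while on PrEP |
|---|---|---|---|---|
| Month 0 | 6 | 33% | 26.7% | 86% |
| Month 3 | 9 | 50% | 40.0% | 84% |
| Month 6 | 12 | 67% | 53.3% | 82% |
| Month 9 | 15 | 83% | 66.7% | 80% |
| Month 12 or later | 18 | 100% | 80.0% | 78% |
| No start | 18 | 100% | 80.0% | 78% |

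Under A, early ART starters look worse than non-starters. Under B, they look better by 4 to 8 points for starts at months 0 to 6. With constant adherence and only PrEP months counted, the result is 80% against 80% and nothing is distorted. The sign therefore depends on the denominator and on whether adherence wanes.

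**4. Does the proposed analysis remove this?** Under B, adherence at month m is 90 − (24/18) × m in both groups. Comparing on-PrEP adherence at the same visit month gives a difference of 0. Counting only PrEP months is not sufficient when adherence wanes; visit month is also needed.

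**The case against.** The strongest reply is that Objective 3.2.1 is an open list of data to collect, not an analysis. It speaks of correlates, pairs none with an outcome, fixes no model, and section 13.1 refers planned analyses to an SAP that is not shown. Timing of covariates, lagging and denominators are ordinary SAP content. Partner ART start is also a sensible correlate of PrEP adherence, since PrEP is meant as a bridge to ART.

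Much of this stands, and it limits the point:

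- A reader might infer that the study will necessarily report false associations, or that starting ART and staying together will look like causes of good adherence. The document does not support that. Apart from ART initiation against ART uptake, size and sign rest on choices it does not make. The stop rule also truncates nothing for ART starts from month 12 (12 + 6 = 18). If most PrEP uptake occurs at enrolment, it precedes separation, and any artefact for uptake is smaller.
- A reader might extend the point to section 13.1, which will assess "The impact of various variables such as age, viral load of partner, region, coital act, use of condom on uptake of PrEP and TasP". That does not hold. Section 11.4 collects index viral load and behavioural information at screening, before PrEP and TasP are offered, so baseline values are a natural reading. The same list also serves seroconversion, for which later values are legitimate.
- Whether members have other partners appears in the same sentence but has neither fault. It can be measured at baseline and at later visits.

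What the reply does not remove is the stated wording. The same sentence dates cohabitation to baseline and then defines another item over the whole of follow-up. An SAP could repair that only by substituting a different variable. Nor can any modelling choice make ART initiation informative about ART uptake.

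**Conclusion.** The point holds in a limited form. The list contains one variable known only at the end of follow-up and one outcome offered as its own correlate; the second is also tied by protocol to the end of PrEP.

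One consequence is certain: ART initiation against ART uptake is 100% against 0%. The others are possible. Staying together throughout can produce spurious associations through retention and length of follow-up. An unadjusted comparison of PrEP adherence by partner ART start can be too high, too low or undistorted. The figures in the tables for separation and adherence rest on assumed rates and show mechanism and direction only; they are not estimates for this study. The 33%, 50% and 67% ceilings follow directly from the Protocol's six-month rule and 18-month follow-up, taking PrEP as started at enrolment. The issue concerns the wording of one secondary objective, which is worth correcting because it is meant to inform counselling.

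**What to change.** Amend Objective 3.2.1 as follows:

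- (a) Remove ART initiation by the index partner as a correlate of ART uptake.
- (b) Replace the item on staying together throughout follow-up with partnership status at baseline for uptake, and with time-updated partnership status from the preceding visit for adherence.
- (c) For PrEP adherence, keep partner ART start, entered as a time-updated covariate; count adherence only while PrEP is supplied; include visit month in the model.

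Nothing in the treatment rules needs to change. The cost is the wording and slightly more analysis work. Quarterly visits (section 11.0) and quarterly questionnaires (Objective 3.2.2) are already planned, so no additional visits are needed. The sponsor should confirm that partnership status and partner ART status are recorded at each of them.

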**Objective 3.2.2: Assess user preferences for ART initiation and PrEP among high-risk HIV-1 serodiscordant couples**

Understanding couples' preferences for and concerns about antiretroviral-based HIV-1 prevention is of utmost importance at this time when guidelines for its use are still being formulated.

Interviewer-administered questionnaires will be used to collect data at baseline and quarterly. The questionnaire will specifically ask about a couple's willingness to use PrEP or ART for prevention and which method is preferred. Data regarding couples' reasons for their choice and their concerns about both methods will be collected both through the questionnaire and through mixed methods.

*The primary outcome of this objective will be data and assessments about serodiscordant couples attitudes towards ART and PrEP as for preventing HIV-1 transmission.*

**Objective 3.2.3: Measure the adherence to PrEP among HIV-1 uninfected partners in serodiscordant couples.**

Understanding adherence to PrEP is a critical research priority, particularly when PrEP is delivered outside of a controlled clinical trial setting and is being used as a bridge to ART for the infected partner. Brief adherence counseling for all participants will be delivered at baseline and then quarterly thereafter. The content of the adherence counseling will be derived from developed counseling messages and procedures defined for this study protocol. The messages will be refined as the project evolves. The role of individual risk aversion and adherence would also be measured (see full details of the study in Protocol C attached)

*The primary outcome of this objective will be data on PrEP adherence. This will be in the form of clinic-based pill counts at follow-up visits and MEMS cap data on how frequently the pill bottle was opened.*

**Objective 3.2.4: Look for evidence of risk compensation by HIV-1 serodiscordant couples on PrEP or TasP.**

Risk compensation when using PrEP occurs when patients, perceiving PrEP to reduce their risk of HIV acquisition, start to engage in riskier behaviors or to reduce their use

of other protection methods such as condoms. Clinical trials on PrEP have not found significant evidence of risk compensation, but the possibility cannot be ruled out in real-world practice.

*The primary measure of this objective is reduction in rate of use of condom per couple on PrEP; and rate of increase in STI diagnosed per couple on PrEP. This data will be generated from the clinical data and the behaviour surveillance data.*

**Objective 3.2.5: Measure the probability of participants developing a resistance to Truvada during the course of the study.**

PrEP and TasP studies have tried to address the issue of drug resistance to tenofovir and emtricitabine. Studies in HIV-1-infected individuals followed small numbers of patients for a short time. Very few cases of resistance have been reported, but participants in these clinical trials are monitored under rigorous clinical trial conditions that do not replicate real world events. Studies in macaques were well designed, but used SHIV, which has an attenuated course of infection. The available information suggests that the probability of emergence of drug resistance is small. Infections that occurred despite use of PrEP had reduced peak viremia, which could reduce HIV transmissibility. Mathematical modeling suggests that, although transmitted drug resistance may under some circumstances increase, the benefits of PrEP outweigh the risks associated with resistance. Tenofovir and emtricitabine are, however, recommended in first-line treatment drugs in Nigeria. It is therefore important to confirm the expected low incidence of drug resistance in daily practice. This demonstration project will conduct a surveillance of drug resistance to Truvada in patients who take PrEP.

*The primary measure of this objective is an estimate of the prevalence of ART resistance that developed in patients who seroconverted while using PrEP.*

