The target population for the demonstration project will be heterosexual serodiscordant couples. Several studies have identified this as a priority population for this kind of intervention, but more than that, enough work has been done with this population in enough places that we now have sociological tools specific to them that we can use with some confidence. WHO, for example, is about to release guidelines for counseling serodiscordant couples about prevention; they will include ART and PrEP as prevention strategies. The study "Partner's PrEP," for another example, developed a simple and effective risk assessment tool that proved to be a good predictor of behaviors in this population. We intend to use it in this project to place participants.

The treatment strategy that will be used in this project adopt both TasP and PrEP. For a serodiscordant couple, PrEP and TasP work together for long-term prevention of HIV infection. ART, necessary for TasP, is not indicated for the infected partner until quite some time after initial diagnosis. Throughout this period, the uninfected partner is at elevated risk. However, if PrEP is adopted by the uninfected partner when the infected partner is diagnosed, that risk is significantly reduced. Eventually the infected partner begins ART

and sometime later achieves viral suppression. At this point as TasP strategy can be adopted and PrEP ended.

To start, a sample with a size of 600 heterosexual HIV-1 serodiscordant couples will be recruited for the study. PrEP would be administered through three sites selected from three States in Nigeria – Anambra, Cross River and Jos.

The project will have three primary goals:

- Construct a model that effectively delivers PrEP to serodiscordant couples. Within the context of this goal, the measure of effectiveness will be the number of new infections averted.
- Measure the cost effectiveness of the model. The measure of cost effectiveness will be cost per life-year gained and cost per infection averted
- Estimate what would be needed to scale up the delivery model to the national level.

Given the data and experience gained from the project, it should be possible to deliver a practical plan, complete with a budget estimate, to scale up PrEP and TasP, and make them part of a comprehensive national HIV prevention package.

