The cost effectiveness question comes up if the infected person is the positive member of a serodiscordant couple. PrEP begins for the uninfected partner as soon as the infected partner is diagnosed and, since the uninfected partner is still uninfected, typically long before the CD4 count of the infected partner begins to decline. Once the infected partner presents an undetectable viral load, the risk of HIV transmission is greatly reduced. If this risk is less than or equal to the risk reduction provided by PrEP, then PrEP could be discontinued for the uninfected partner with no increase in risk. (The prevention strategy

---

after this point is called "Treatment as Prevention" or TasP.) PrEP is, therefore, a continuous cost from the moment of the diagnosis of the infected partner until six months after the infected partner starts ART. Under current guidelines that is six months after the infected partner's CD4 count falls to 350.

In the chart (Figure 1), the vertical dashed line is set at about 75%, which was the efficacy of the FTC / TDF method of PrEP found in the Partner's PrEP study. If viral suppression after ART in the infected partner protects the uninfected partner at least this effectively, then PrEP can be discontinued in favor of TasP and the differential costs saved.

This raises a question. Once started, ART becomes a continuous lifetime cost. If the infected partner is going to start ART at some point anyway, could the same risk reduction as PrEP have been bought for this couple at less total cost by starting ART at a CD4 count greater than 350? In other words, is it more cost effective to start ART earlier, thereby moving to TasP earlier, and save the expense of PrEP over the shortened period of high risk to the uninfected partner?

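### Objective 3.2.4 asks about risk compensation on PrEP or TasP, but its primary measure covers only couples on PrEP and, read literally, omits the period after PrEP stops

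*Protocol*

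**What the plan says.** The protocol states the scope of the objective twice. The list in section 3.2 reads "Look for evidence of risk compensation by HIV-1 serodiscordant couples on PrEP or TasP, migration from condom use", and the detailed heading repeats "Look for evidence of risk compensation by HIV-1 serodiscordant couples on PrEP or TasP". The primary measure given under that heading is "reduction in rate of use of condom per couple on PrEP; and rate of increase in STI diagnosed per couple on PrEP", to be drawn from clinical data and behaviour surveillance.

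The move from one strategy to the other is part of the design. Section 2.0 says that "if the HIV-1 infected partner initiates ART, we will discontinue PrEP for the HIV-1 uninfected partner six months later", and section 11.5 says the same: "Once the HIV-1 infected partner has been using ART for 6 months, PrEP will be discontinued for the HIV-1 uninfected partner". The Summary describes the switch as "At this point as TasP strategy can be adopted and PrEP ended", and section 1.4 says that the strategy "after this point is called 'Treatment as Prevention' or TasP". ART is widely available in the study; section 11.5 states: "All HIV-1 infected partners who are interested in starting ART independent of their becoming eligible for ART under the current national guidelines, will be offered" it.

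Behaviour data are not tied to PrEP use. Section 11.5 has both partners interviewed during follow-up, with risk compensation among the topics. Section 14.3 has risk-behaviour data collected from every participant.

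**The concern.** The objective names two strategies and the measure names one. A couple that follows the planned path is counted while the uninfected partner takes PrEP. Once PrEP ends and protection rests on the index partner's ART alone, a literal reading no longer counts the couple. A couple in which the index partner takes ART and the other partner never takes PrEP is not counted at all.

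The post-switch period is where one would want to know whether condom use falls or STI diagnoses rise once PrEP has been withdrawn. No other section supplies a risk-compensation measure for it. Section 13.1 mentions condom use only as a factor that may affect uptake and seroconversion. An analysis that follows the stated measure would therefore report on only part of what the objective asks.

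**Working it through.** The protocol gives no figure to reproduce here. The check is a comparison of the text by treatment phase, followed by simple arithmetic on time.

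**Coverage by phase**

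| Phase | In the objective? | In the measure, read literally? |
|---|---|---|
| PrEP, index partner not on ART | Yes | Yes |
| PrEP and ART together (up to six months) | Yes | Yes |
| ART after PrEP has stopped | Yes (TasP) | No |
| ART, PrEP never taken | Yes (TasP) | No |

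The protocol uses TasP in two senses. The Summary and section 1.4 mean the strategy after suppression, when PrEP has ended. Sections 11.5 and 11.11 speak of offering or opting for TasP, which makes it begin with ART use. The last two rows fall outside the measure in either sense. The second row is covered in either sense.

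**Share of one couple's follow-up that is omitted**

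Inputs:
- Follow-up of up to 18 months (section 11.0), taken here at its full length.
- PrEP stops six months after ART starts (sections 2.0 and 11.5).
- *t* is the month after enrolment at which ART starts. The protocol gives no distribution for it.

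Formula: omitted share = max(0, 18 − (*t* + 6)) / 18.

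| *t* (months) | Omitted months | Share |
|---|---|---|
| 0 | 12 | 12/18 = 67% |
| 3 | 9 | 9/18 = 50% |
| 6 | 6 | 6/18 = 33% |
| 12 or later | 0 | 0% |

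Sections 2.0 and 7.3 allow some index partners to be on ART already at entry, and for them the share could exceed 67%. Couples whose index partner never starts ART, or starts and stops before the switch, remain on PrEP and lose nothing.

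**Share across all couples**

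Suppose a fraction *f* start ART at enrolment, and no others start early enough to reach the switch. The omitted share is then *f* × 12/18.
- *f* = 20%: 0.20 × 12/18 = 13%.
- *f* = 50%: 0.50 × 12/18 = 33%.

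Neither value of *f* is a protocol figure for this study. The only ART-uptake figure in the document is in section 1.4: 20% of index partners over a median of 23 months in the cited PrEP efficacy trial. Those index partners did not meet treatment guidelines at enrolment, whereas ART is offered to all here, so higher uptake is plausible. If 20% started gradually and not all at enrolment, the share would be below 13%. Further starts before month 12 would add to either figure.

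**The case against.** Several points on the other side have force.

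*The study could still report on TasP.* The protocol names a primary measure, not the only one. It collects behaviour data from everyone and defers the detailed analyses to an SAP. A reader might infer from the mismatch that the study cannot answer the TasP part of its objective at all. The documents do not support that: the data would exist, and a further tabulation is not forbidden. What stands is that the protocol itself fixes a measure narrower than its objective, so an SAP that simply follows it inherits the gap.

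*Some TasP time is already counted.* This is correct. The PrEP-plus-ART overlap stays in, so it would be wrong to say that all time on TasP is excluded.

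*The phrase about couples on PrEP may be a loose label for couples who took PrEP in the project.* This is possible, since the text has no explicit rule that ends counting at the switch. But it does not state that meaning either. That reading would still omit couples using ART without PrEP and would not separate behaviour before the switch from behaviour after it.

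*The changing mix of couples.* Because PrEP continues where ART is declined or stopped, couples still on PrEP late in follow-up will increasingly be those not on sustained ART. A reader might infer that any trend in the measure is distorted by this. That follows only if the measure is a rate over time on PrEP. If the reduction per couple means change within each couple, the departure of other couples does not by itself create a trend.

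*The size is uncertain.* This is also correct. Eighteen months is a maximum, and sections 11.0 and 11.4 disagree on accrual (about 6 against about 12 months). With 12 months of follow-up, a start at enrolment would leave (12 − 6)/12 = 50% outside the measure, not 67%.

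*The heading could be narrowed instead.* The rationale under the objective discusses only PrEP, so deleting TasP from the objective would also remove the mismatch. It would, however, give up a question that the planned data can address.

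**Conclusion.** The mismatch is real and nothing else in the protocol resolves it. Read literally, the primary measure of Objective 3.2.4 omits the period after PrEP is stopped and couples who use ART without PrEP, while it keeps the overlap.

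For one couple with full follow-up, the loss runs from none to 67% for ART starts from month 12 or later back to enrolment. The shares across all couples, 13% and 33%, rest on assumed starting fractions of 20% and 50% and illustrate scale only. They should not be read as an estimate that a third of couple-time will be lost. The contradiction between objective and measure depends on none of these numbers.

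Only a secondary, exploratory objective is touched. Sample size, the primary objectives and data collection are unaffected. The change is worth making because it lets the study answer its own question at almost no cost.

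**What to change.** Reword the primary measure of Objective 3.2.4 so that it covers all enrolled couples on PrEP or TasP. Report the change in condom use and in STI diagnoses from the couple's own enrolment value, separately for three phases:
- PrEP without ART;
- PrEP plus ART;
- ART after PrEP has stopped, or without PrEP.

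Say whether a couple is classified by its current phase or by ever having taken PrEP; the three phases call for current phase. If the existing wording was meant as time on PrEP, the comparison with the couple's own enrolment value also guards against the changing mix of couples who remain on it.

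The cost is one wording change and a time-varying phase variable built from recorded PrEP and ART dates. The planned interviews and clinical records supply the outcomes, so no new data are needed and no treatment rule changes.
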